Nowadays, machine learning algorithms are increasingly used in medicine and especially in pharmacology to predict the exposure to a drug, the initiation dose or the interval between two infusions. We have developed a machine learning algorithm to predict the risk of rituximab underdosing.^24^ Based on age, sex, body surface area, anti-PLA2R1 antibody titre at day 0, serum albumin at day 0 and at day 15 and serum creatinine at day 0 and at day 15, this algorithm demonstrated its ability to predict rituximab underdosing at 3 months with an accuracy, sensitivity and specificity of, respectively, 79.4%, 78.7% and 81.0%. To validate the clinical relevance of our algorithm, we analysed the outcome of 45 patients with membranous nephropathy treated with rituximab. We retrospectively analysed the cumulative doses of rituximab received to achieve clinical remission and the time to achieve clinical remission according to the initial probability of rituximab underdosing proposed by our algorithm. Patients with a high initial probability of rituximab underdosing (>50%) had a longer time to remission (probability of rituximab underdosing ≤50%: 4.2±1.8 months vs 51%–75%: 8.4±4.6 months vs >75%: 10.7±5.9 months; p=0.002) and received higher cumulative doses of rituximab (probability of rituximab underdosing ≤50%: 2.0±0.0 g vs 51%–75%: 2.7±0.9 g vs >75%: 3.6±1.6 g; p=0.001).^24^

To prospectively evaluate our algorithm, we planned a multicentre, randomised study to evaluate the superiority and safety of an algorithm-guided rituximab regimen versus a standard regimen in patients with membranous nephropathy.

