### Machine learning algorithm

A machine learning algorithm was developed to predict the risk of rituximab underdosing (concentration <2 µg/mL at month 3).^24^ The algorithm is based on a support vector machine (SVM) with a polynomial kernel and was selected after comparison with several supervised models, including logistic regression, random forests and artificial neural networks. The SVM was chosen for its ability to handle data with small sample sizes while maximising the separation between classes in a high-dimensional space.

The performance of the models was assessed by 10-fold cross-validation on the training set (75% of the data). The SVM achieved an accuracy of 79.4%, outperforming logistic regression (70.6%), random forests (73.5%) and artificial neural networks (68.3%). In terms of sensitivity and specificity, the SVM showed a balanced performance (84.6% and 72.7%, respectively, on the test set) compared with the results obtained by logistic regression (sensitivity 75% and specificity 65%) and random forests (sensitivity 78.1% and specificity 68.2%). The SVM also showed an F-score of 81.5%, highlighting its overall effectiveness in categorising patients.

The model’s input variables were selected using a forward-backward approach, systematically assessing the impact of adding or removing a variable on predictive performance. The variables selected included age, sex, body surface area (BSA), anti-PLA2R1 antibody titre at day 0 (optional variable), serum albumin and serum creatinine at days 0 and 15. Prior to model training, data were preprocessed with K-nearest neighbour imputation of missing values, followed by standardisation to ensure homogeneous scaling of continuous variables.

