### Treatment arms

#### Experimental strategy

For patients randomised to the experimental arm, the iRITUX multidisciplinary staff will run the algorithm and make a recommendation to the referring nephrologist based on the risk of rituximab underdosing at month 3.

Patients with a risk between 0% and 50% will receive 1 g×2 (day 0 and day 15).Patients with a risk between 51% and 75% will receive 1 g×3 (day 0, day 15 and day 30).Patients with a risk between 76% and 100% will receive 1 g×4 (day 0, day 15, day 30 and day 45).

If the opinion of the referring nephrologist contradicts the result generated by the iRITUX algorithm, the opinion of the patient’s treating nephrologist will prevail in all cases.

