#### Control strategy

Patients randomised to the control arm will receive two courses of rituximab at a dose of 1 g on days 1 and 15.

To improve compliance, patients will be contacted by telephone before each treatment. A medical consultation is also scheduled for all rituximab injections.

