### Evaluation criteria

The primary endpoint is the clinical remission 6 months after the first rituximab infusion. Clinical remission is defined as a composite criterion, combining according to KDIGO guidelines: (1) complete clinical remission, defined as urinary protein/creatinine ratio (UPCR) <0.3 g/g in a morning spot urine sample and serum albumin >30 g/L and (2) partial clinical remission, defined as UPCR <3.5 g/g with a decrease >50% from baseline (ie, first rituximab infusion) and improvement or normalisation of serum albumin.

Secondary endpoints include complete clinical remission at month 12; partial clinical remission at month 12; immunological remission (ie, negative antibody titre by ELISA or negative indirect immunofluorescence) at month 3, month 6, month 9 and month 12; changes in proteinuria and albuminuria from baseline to month 3, month 6, month 9 and month 12; changes in serum creatinine and CKD-EPI estimated glomerular filtration rate from baseline to month 3, month 6, month 9 and month 12; changes in anti-PLA2R1 antibody ELISA titre from baseline to month 3, month 6, month 9 and month 12 (patients with PLA2R1-associated membranous nephropathy only); occurrence of anti-rituximab antibodies at month 3, month 6, month 9 and month 12; residual serum rituximab level at month 3 after the first rituximab infusion; recording adverse events related to treatment during study follow-up; changes in lymphocyte counts: B cells (CD19, transitional, mature and memory) and T cells (CD3, CD4, CD8 and T-Reg); changes in non-immunosuppressive antiproteinuric treatment during study follow-up; assessment of clinician satisfaction with the algorithm used to calculate the risk of rituximab underdosing (in the experimental group only); predictive rate (%) of the algorithm for rituximab underdosing in the control group; pharmacokinetics in all patients with serum creatinine and serum albumin levels, weight, anti-PLA2R1 and rituximab level at day 0, day 15, day 30, day 45, month 3 and month 6; and plasma cytokine levels after non-specific stimulation of innate and adaptive immunity cells in pg/mL (interferon (IFN)-γ, IFN-α, interleukin (IL)-12p70, IL-17A, IL-4, IL-5, IL-10, IL-1 and IL-6) at day 0 and month 6.

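### The algorithm's low-risk call is checked in control patients only; adding two-infusion patients at ≤50% risk from the experimental arm would about double the data on its negative predictive value

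*Protocol article*

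**What the plan says.** The Evaluation criteria section of the protocol article gives the algorithm's prospective check as the "predictive rate (%) of the algorithm for rituximab underdosing in the control group". The Machine learning algorithm section describes the model as built to "predict the risk of rituximab underdosing (concentration <2 µg/mL at month 3").

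The Experimental strategy section states: "Patients with a risk between 0% and 50% will receive 1 g×2 (day 0 and day 15"). The Control strategy section states: "Patients randomised to the control arm will receive two courses of rituximab at a dose of 1 g on days 1 and 15". The Abstract puts the first control infusion on day 0, so these two places need to be reconciled. Both describe two 1 g infusions.

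The month-3 level is collected in both arms. Evaluation criteria lists the "residual serum rituximab level at month 3 after the first rituximab infusion" without limiting it to an arm, and also "pharmacokinetics in all patients with serum creatinine and serum albumin levels, weight, anti-PLA2R1 and rituximab level at day 0, day 15, day 30, day 45", continuing to month 3 and month 6.

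The experimental regimen is not binding. If the referring nephrologist disagrees with the algorithm, "the opinion of the patient’s treating nephrologist will prevail in all cases".

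**The concern.** The ≤50% call is the one on which the experimental strategy stays with two infusions. Its error rate, the share of patients called low risk who are nevertheless below 2 µg/mL at month 3 (1 − NPV), shows whom the algorithm misses. A patient called low risk and given two infusions can inform that rate in either arm. The risk is computed from day-0 and day-15 values, before the planned regimens diverge, and the outcome is the same laboratory level at month 3. As worded, the endpoint uses only the control half of these patients.

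What is at stake is precision. The protocol's own performance figures suggest that the miss rate may not be small, and the control arm alone estimates it loosely.

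**Working it through.** **Inputs.** N = 130 including 5% loss (Sample size); 1:1 allocation (Randomisation), so 65 per arm. The protocol gives no precision target for this endpoint, so there is no stated figure for it to reproduce. The total of 130 is close to what the stated assumptions give: 117.7 (average-proportion variance) × 1.024 (O'Brien-Fleming inflation) / 0.95 = 127. It is used as stated.

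**Step 1: share called low risk and NPV.** Neither is stated, so both are inferred. From accuracy = sens × π + spec × (1 − π), the prevalence of underdosing is π = (spec − acc)/(spec − sens).

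- Introduction ("predict rituximab underdosing at 3 months with an accuracy, sensitivity and specificity of, respectively, 79.4%, 78.7% and 81.0"%): π = (0.810 − 0.794)/(0.810 − 0.787) = 0.696. Low-risk share = 0.213 × 0.696 + 0.810 × 0.304 = 0.394. NPV = 0.246/0.394 = 0.62, so the miss rate is about 38%. Rounding of the published percentages alone moves NPV between about 57% and 67%.
- Machine learning algorithm section (test-set sensitivity 84.6%, specificity 72.7%, accuracy 79.4%): π = (0.794 − 0.727)/(0.846 − 0.727) = 0.563. Low-risk share = 0.154 × 0.563 + 0.727 × 0.437 = 0.404. NPV = 0.318/0.404 = 0.786, so the miss rate is about 21%. This assumes that the accuracy belongs with the test-set values.

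Both give a low-risk share near 40%. As this is an inference, 20% to 70% is shown below.

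**Step 2: precision.** Half-width = 1.96 × √(p(1 − p)/n), with n = share × 65 (control only) or share × 130 (both arms, no overrides).

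| Low-risk share | n, control → both | Miss rate 21.4% | Miss rate 38% |
|---|---|---|---|
| 20% | 13 → 26 | ±22.3 → ±15.8 | ±26.4 → ±18.7 |
| 40% | 26 → 52 | ±15.8 → ±11.1 | ±18.7 → ±13.2 |
| 70% | 46 → 91 | ±11.9 → ±8.4 | ±14.0 → ±10.0 |

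Half-widths are in percentage points. Doubling n narrows the interval by 1 − 1/√2 = 29% at any share. With 5% loss (61.75 per arm) and a 40% share, n goes from 25 to 49, and the half-width at a miss rate of 21.4% from ±16.1 to ±11.5.

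**Step 3: overrides.** If a fraction o of low-risk experimental patients is moved off two infusions, the experimental arm supplies (1 − o)/(2 − o) of the usable low-risk patients: 50% at o = 0, 47% at 10%, 41% at 30%. The override rates are assumptions.

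A worst case counts every overridden patient as underdosed. With 26 low-risk patients per arm:

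- Miss rate 21.4%: (0.214 × 49.4 + 2.6)/52 = 25% at 10% override; (0.214 × 44.2 + 7.8)/52 = 33% at 30%.
- Miss rate 38%: (0.38 × 49.4 + 2.6)/52 = 41% at 10% override; (0.38 × 44.2 + 7.8)/52 = 47% at 30%.

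Few overrides leave the gain intact. Many could shift the estimate by about as much as the half-width.

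**Step 4: why pooling must stop at the NPV.** Adding the experimental low-risk patients without weights counts low-risk calls twice as often as high-risk calls. With the test-set values, sensitivity would read 0.846/(0.846 + 2 × 0.154) = 73.3% instead of 84.6%, and specificity 2 × 0.727/(2 × 0.727 + 0.273) = 84.2% instead of 72.7%. The NPV conditions on the low-risk call and is not distorted in this way. Even with correct weighting, overall accuracy gains little: about ±10.1 to ±9.0 points with 62 per arm.

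**The case against.** The control-only restriction is sound. No other group has all risk bands planned on one regimen, so only there are sensitivity, specificity, positive predictive value and accuracy free of algorithm-driven dosing. This stands in full. A reader might infer that the restriction is an error; the document does not support that.

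A reader might also infer that the experimental low-risk data are thrown away. They are not: they are collected and reported under the month-3 level and pharmacokinetic endpoints. Those endpoints, as worded, do not set predicted against observed underdosing. Nor does the loss of about half extend beyond the low-risk call. At a 40% share the control arm already holds 65 of 91 patients planned for two infusions (65 + 26), or 71%.

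It is tempting to say that a single percentage conceals the NPV. The article does not define the predictive rate or exclude a breakdown, and such detail may properly sit in the full protocol or analysis plan. No finding rests on that.

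The strongest objection is selection. Two infusions are not assured at ≤50% risk, because the nephrologist may override. Setting overridden patients aside is selection after randomisation. If clinicians add doses for patients they judge undertreated, the pooled NPV would be biased upward, and the control arm has no recommendation to override. This stands as a limit on the added estimate. It is why that estimate should be supplementary, shown beside the control-only result, and bounded.

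**Conclusion.** The point holds as a minor improvement to a secondary endpoint. For the low-risk call, about half of the patients who could inform the NPV are not used for this endpoint (41–47% of the usable ones if 10–30% are overridden). Using them would cut the 95% half-width from about ±16–19 to about ±11–13 points.

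These sizes assume a low-risk share near 40%, a miss rate of 21% to 38% inferred from the published performance figures, and 65 patients per arm. The relative gain of 29% depends only on 1:1 allocation and few overrides. The primary endpoint, alpha, sample size and data collection are unaffected.

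**What to change.** Keep the control-group analysis as the main one, including sensitivity, specificity, positive predictive value and accuracy. Before data are seen, add one supplementary estimate: the observed rate of month-3 rituximab <2 µg/mL (1 − NPV), with its 95% interval, among all patients in both arms with predicted risk ≤50% who received two infusions. Show it beside the control-only estimate.

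Report the number and month-3 levels of low-risk experimental patients whose recommendation was overridden, with a sensitivity analysis counting them as underdosed. Do not carry the pooled patients unweighted into any overall measure. Reconcile the day of the first control infusion between the Abstract and the Control strategy section.

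The cost is a line or two of wording and a little extra analysis, with no new sample or visit. The remaining downside is possible selection from overrides, which the sensitivity analysis makes visible but does not remove.

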### Safety data

We will record any adverse medical events in the form of signs, symptoms, abnormal laboratory results or conditions that occur or worsen compared with the baseline. The study sponsor (Nice University Hospital) has purchased insurance for this trial and is responsible for reporting adverse events to the European Medicines Agency.

As rituximab (Truxima®) is an approved treatment by the European Medicines Agency and the US Food and Drug Administration, we do not anticipate significant or serious adverse events. As a result, a data safety monitoring board is not required during the trial.

### Follow-up

Study visits will be performed on day 15, day 30, day 45, month 3, month 6, month 9 and month 12 after the first dose (day 0) of rituximab for routine follow-up.

Clinical assessments (weight, blood pressure, heart rate, presence of oedema and change in concomitant medications) and biosamples will be collected at all follow-up visits, including a shipment to the central laboratory at each follow-up visit.

An individual participant may be discontinued from study intervention in the following

situations:

Participant decision. The participant is at any time free to discontinue treatment, without prejudice to further treatment.An adverse event that, in the opinion of the investigator, warrants discontinuation.

In the event of premature discontinuation of treatment, the patient should be encouraged to comply with protocol evaluations to allow intention-to-treat (ITT) analyses.

### Data collection

The study data will be collected in an e-CRF. This will be implemented by the data manager using the RedCap software. The parameter specification and the implementation of the e-CRF for data collection, including user training, will be provided by the designated data manager.

The investigators and the clinical research assistants at each site will be responsible for collecting and entering data directly into the e-CRF. The data will be securely stored, with specific access rights granted to study teams according to their role.

Data quality control will be performed on the e-CRF, using the patient medical file, by the sponsor during the planned monitoring visits by the Department of Clinical Research and Innovation’s Clinical Research Officer.

Once the final data have been entered, checks for their validity and coherence will be performed by the Data Manager of the Department of Clinical Research and Innovation, and requests for verification will be issued. Throughout the study, any modifications to the database will be recorded, enabling a full audit trail.

At the end of the quality control process, the database will be frozen and signed off by the PI, the data manager and the methodologist. No modification of the data will be possible after this time.

The frozen database, together with the data management report, will then be transferred to the statistician for analysis.

### Data monitoring committee

The data monitoring committee is composed of three research assistants in charge of on-site monitoring, supervised by the iRITUX project manager from the Clinical Research and Innovation Department of the Nice University Hospital.

### Statistical methods

Our analysis strategy will consider two populations.

ITT population: all patients included in the control or experimental group, whether or not they completed the treatment schedule and had all the biological samples required by the protocol. For the ITT analysis, and in the case of a significant number of lost to follow-up patients (estimated to be 5% for the protocol) that would challenge the robustness of the result, the ‘last observation carried forward’ strategy will be used to impute the missing data for the primary objective.Per-protocol (PP) population*:* all patients enrolled in the study who completed the treatment schedule and had all the biological samples required by the protocol.

As indicated in the sample size calculation, three interim efficacy analyses will be performed. The aim of these interim analyses is to demonstrate the positive effect of increasing the rituximab dose according to the patient’s risk level on the remission rate in order to apply this algorithm as soon as possible.

To maintain the alpha risk at 0.025 with a beta risk equal to 0.2 for the final analysis and to limit the possibility of a chance of a positive interim finding, each interim analysis was planned with:

A one-sided significance level of 0.0002248 was allotted to the first efficacy interim analysis (n=44).A one-sided significance level of 0.00209 was allotted to the second efficacy interim analysis (n=66).A one-sided significance level of 0.00969 was allotted to the third efficacy interim analysis (n=98).A one-sided significance level of 0.02144 was retained for the final analysis (n=130).

The rate of clinical remission observed at 6 months from the first rituximab injection (primary outcome) in the two groups will be compared with access to the significance level, applying a one-sided test for the difference between two binomial proportions (χ^2^ test or Fisher’s exact test in case of a small sample). As the experimental and control groups differ only in the dose of rituximab, with a higher or equivalent dose in the experimental group, a two-sided test is unnecessary in our study.

In case of a statistically significant result at an interim analysis (p value under significance level), the independent committee will decide the termination of the trial (the interim analysis becomes the main analysis). Any retreatment with immunosuppressive therapy (including rituximab) not planned in the protocol before the end of the study at month 12 will be considered a treatment failure (ie, absence of remission). The statistical tests used, parametric or non-parametric, will consider the total number of patients and the distribution of the variables collected.

For secondary objectives, rates of complete and partial clinical remission at month 12 will be compared using a one-tailed test for the difference between two binomial proportions. Changes in biological samples at 3, 6, 9 and 12 months will be evaluated first by analysis of variance if the normal distribution hypothesis is met and second by a paired Student’s t-test or non-parametric Wilcoxon’s S-rank test, as recommended. For longitudinal analyses, secondary outcomes will be analysed using a linear mixed model to account for repeated measures, including fixed effects for time and intercept random effects for patients. The variables of interest and adjustment will be primarily age and sex, given the total number of patients and the distribution of the variables collected.

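### The per-protocol set requires every protocol sample through month 12, so it can drop patients whose month-6 primary outcome is fully evaluable

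*Protocol article*

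**What the plan says.** The Statistical methods section of the protocol article names two analysis populations. The ITT population keeps every included patient "whether or not they completed the treatment schedule and had all the biological samples required by the protocol". The PP population is "all patients enrolled in the study who completed the treatment schedule and had all the biological samples required by the protocol". The same sample condition is waived in one definition and imposed in the other.

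The Follow-up section shows which samples are meant: "Study visits will be performed on day 15, day 30, day 45, month 3, month 6, month 9 and month 12", and "biosamples will be collected at all follow-up visits, including a shipment to the central laboratory at each follow-up visit". Evaluation criteria adds samples for mechanistic and pharmacokinetic endpoints, among them stimulated cytokines, lymphocyte subsets and rituximab levels at days 30 and 45.

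On the primary outcome, Evaluation criteria says: "The primary endpoint is the clinical remission 6 months after the first rituximab infusion". Complete and partial remission are both defined from UPCR and serum albumin, with change measured from the first infusion.

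**The concern.** A PP analysis is meant to show the effect in patients who were treated as planned and whose outcome can be judged. Here membership also depends on samples that play no part in judging the primary outcome. Some are taken after that outcome has been recorded (months 9 and 12). Others are taken earlier, or at month 6 itself, for other purposes.

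Two things are at stake. Patients with a complete month-6 outcome are discarded, which costs precision. In addition, the month-6 comparison is conditioned on attendance after month 6, which may itself depend on whether the patient responded. If PP and ITT then disagreed, the reader could not tell whether treatment adherence or sample collection was the cause.

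**Working it through.** **The plan's own figure.** The sample size assumes 75% versus 50% remission, one-sided alpha 0.025, power 0.80, four looks and 5% loss.

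- Fixed design with pooled variance, per arm: (1.960 + 0.842)² × 2 × 0.625 × 0.375 / 0.25² = 58.87, so 117.7 in total.
- With the O'Brien-Fleming inflation factor of 1.0245 for looks at 44, 66, 98 and 130: 117.7 × 1.0245 = 120.6.
- With 5% loss: 120.6 / 0.95 = 127.0, within 3% of the stated 130.

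The four stated significance levels give an overall alpha of 0.0249. No stated figure is wrong; the point concerns only the definition of the PP set.

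**Samples required against samples needed.** There are seven post-baseline visits. The primary outcome needs one of them (month 6). Four come earlier (days 15, 30 and 45, and month 3) and two come later (months 9 and 12).

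**Effect on the size of the set.** The documents give no completeness rate, so let q be an assumed probability that a visit's samples are complete, independent across visits, with baseline complete. Exclusions for incomplete treatment are the same under both rules and are left out.

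- Current rule: 130 × q⁷
- Month-6 sample only: 130 × q
- Patients removed only because of a month-9 or month-12 sample: 130 × (q⁵ − q⁷)
- Ratio of standard errors, current rule to month-6 rule: √(q / q⁷) = q⁻³

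| q | Current rule | Month 6 only | Removed only for months 9/12 | Ratio of standard errors |
|---|---|---|---|---|
| 0.99 | 130 × 0.932 = 121 | 129 | 130 × (0.951 − 0.932) ≈ 2 | 1.03 |
| 0.98 | 130 × 0.868 = 113 | 127 | 130 × (0.904 − 0.868) ≈ 5 | 1.06 |
| 0.95 | 130 × 0.698 = 91 | 123–124 | 130 × (0.774 − 0.698) ≈ 10 | 1.17 |

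**If missingness is clustered.** Suppose the only missing data come from the planned 5% of patients, all lost before month 6. Both rules then keep 130 × 0.95 = 123.5 patients and the definition costs nothing. The table therefore shows what independent misses would do. It is not a forecast.

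**The case against.** **The main comparison is not touched.** This stands. ITT ignores the sample condition, and it alone carries the imputation rule for the primary objective. A reader might infer that the primary result is at risk; the documents do not support that. Nor is it a finding that PP is not labelled supportive, since a protocol article may leave that to the full protocol or the SAP.

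**Missed samples are non-adherence, and one strict set can serve both month-6 and month-12 endpoints.** The first half is fair: the samples are required by the protocol. But a missed month-9 sample says nothing about whether the month-6 outcome followed the planned treatment, and selection on later attendance is not made harmless by being strict.

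**The size is assumed.** This also stands. Independent misses exaggerate the loss if the same patients miss several visits, and the protocol expects close follow-up with 5% loss.

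**Interim analyses.** A reader might infer that the rule also excludes recently assessed patients at every interim look, because "three interim efficacy analyses will be performed" and, after a significant one, "the interim analysis becomes the main analysis". The documents do not establish this. They do not say that PP is analysed at an interim, or whether n = 44, 66 and 98 counts patients enrolled, at month 6 or at month 12. Unplanned retreatment before month 12 counts as failure, so month-12 follow-up might be needed in any case. Only if PP is analysed at the interims and n counts month-6 outcomes would patients between months 6 and 12 be lost. Under uniform accrual over 72 months that is 130 / 72 × 6 ≈ 11 patients at each look (25% of 44, 16% of 66, 11% of 98).

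**Unequal infusion counts.** Up to four infusions against two could make completion harder in the experimental arm. Under illustrative assumptions (half the patients high-risk, 75% remission in low-risk and 50% in high-risk patients, no treatment effect, 80–90% of high-risk experimental patients completing) the bias is about 0.7–1.4 percentage points. That is small, and any set that requires the assigned schedule would share it. It is not part of this point.

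**Conclusion.** The point holds as a minor defect in a rule that the article states outright. The PP set is not tied to the endpoint it will be used for. For the month-6 primary endpoint it can remove patients whose outcome is fully evaluable, and it selects on follow-up after that outcome.

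The size depends on sample completeness, which the documents do not give. Against a month-6 requirement, the set loses about 8 patients (129 − 121) at 99% per-visit completeness, about 14 (127 − 113) at 98% and about 32–33 (123–124 against 91) at 95%, under independence. The loss would be smaller, possibly nil, if missing samples cluster in the same patients. ITT, the sample size and the significance levels are unaffected, and an effect at the interim looks is conditional on facts that the documents do not state.

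**What to change.** Replace the sample condition in the PP definition with an endpoint-specific one. For the primary endpoint: patients who completed their assigned infusion schedule and have evaluable UPCR and serum albumin at baseline and month 6, with no requirement for samples that this outcome does not use. For month-12 endpoints: the same treatment condition with the corresponding month-12 data.

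Day-15 serum albumin and creatinine are inputs to the algorithm. If the sponsor wants them to count in the experimental arm, they belong under the assigned-schedule condition and not under a general sample rule.

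The cost is one sentence in the analysis populations. It needs no new data, visits or patients. The change should be made before the first interim analysis, so that the definition is settled before any outcome comparison is seen.

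### The per-protocol set asks for more infusions from high-risk patients in the algorithm arm than from anyone in the control arm, so it preferentially removes poor-prognosis patients from the algorithm arm

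*Protocol article*

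**What the plan says.** The Statistical methods section names two analysis populations. ITT keeps all included patients "whether or not they completed the treatment schedule and had all the biological samples required by the protocol". Per-protocol is "all patients enrolled in the study who completed the treatment schedule", with the further condition that every required sample is available. One definition serves both arms, and the two populations are not explicitly ranked.

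What has to be completed differs by arm:

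- Control strategy: "Patients randomised to the control arm will receive two courses of rituximab", whatever their risk.
- Experimental strategy, lowest class: "Patients with a risk between 0% and 50% will receive 1 g×2".
- Experimental strategy, middle class: "Patients with a risk between 51% and 75% will receive 1 g×3".
- Experimental strategy, highest class: "Patients with a risk between 76% and 100% will receive 1 g×4 (day 0, day 15, day 30 and day 45".

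The Introduction reports on prognosis by predicted risk: "Patients with a high initial probability of rituximab underdosing (>50%) had a longer time to remission". Mean times to remission were 4.2, 8.4 and 10.7 months in the three risk classes.

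**The concern.** Completing the schedule is a post-randomisation condition. Here it is stricter in one arm, and within that arm it is stricter for the patients expected to remit more slowly. A high-risk patient who stops after the second infusion leaves the per-protocol set if allocated to the algorithm. The same patient allocated to control has completed treatment and stays, provided all samples are available. The two per-protocol arms then differ in case mix, with relatively fewer high-risk patients on the algorithm side.

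At stake is how the supportive analysis is read. A per-protocol difference somewhat larger than the ITT difference would look like confirmation that the full algorithm regimen works, when part of it could be selection.

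**Working it through.** The plan gives no figure for the per-protocol set, so there is nothing to reproduce. The yardstick is the planned difference in the Sample size section: 75% − 50% = 25 points.

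**Inputs.** From the document: the schedules by arm and the direction of prognosis. Assumed, because the document does not give them:

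- share at risk >50%: h = 0.60
- month-6 remission: 0.40 in high-risk and 0.75 in other patients
- no effect of the added infusions
- all controls and all low-risk algorithm-arm patients complete
- a fraction d of high-risk algorithm-arm patients does not complete, with d from 5% to 30%
- remission among non-completers, r: either 0.40 (average for their class) or 0.20 (worse than their class)

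The lower end, d = 5%, borrows the plan's only attrition figure. That figure is loss to follow-up, not infusion completion.

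**Formulae.**

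Control rate = 0.60 × 0.40 + 0.40 × 0.75 = 0.540.

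Algorithm-arm per-protocol rate = [0.60 × (0.40 − d·r) + 0.40 × 0.75] / [0.60 × (1 − d) + 0.40].

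**Results.** The true difference is 0 throughout.

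| d | Rate, r = 0.40 | Difference (points) | Rate, r = 0.20 | Difference (points) |
|---|---|---|---|---|
| 5% | 0.528/0.97 = 0.544 | +0.4 | 0.534/0.97 = 0.551 | +1.1 |
| 10% | 0.516/0.94 = 0.549 | +0.9 | 0.528/0.94 = 0.562 | +2.2 |
| 20% | 0.492/0.88 = 0.559 | +1.9 | 0.516/0.88 = 0.586 | +4.6 |
| 30% | 0.468/0.82 = 0.571 | +3.1 | 0.504/0.82 = 0.615 | +7.5 |

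**Letting controls drop out too.** Suppose an equal 5% loss at each infusion in both arms. Completion is 0.95² = 90% for two infusions, 0.95³ = 86% for three and 0.95⁴ = 81% for four. With 50/25/25% of patients in the risk classes, the bias is:

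- remission 75/50/50%: 0.630 − 0.625 = +0.5 points
- remission 75/50/25%: 0.571 − 0.5625 = +0.9 points

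With a 10% loss per infusion the same two cases give +1.0 and +1.8 points. The direction is unchanged and the size is small.

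**What adjustment for the score can do.** Return to the first model and standardise the per-protocol rates to the ITT risk mix. The remaining bias is 0.60 × [(0.40 − d·r)/(1 − d) − 0.40]. For r = 0.40 this is 0. For r = 0.20 it is 0.12·d/(1 − d), which is +0.6, +1.3, +3.0 and +5.1 points for d = 5, 10, 20 and 30%. More than half of the bias in the right-hand column stays.

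**The case against.** The strongest reply has five parts.

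- **Controls are removed too.** The definition also demands all samples, and visits with biosamples at days 30 and 45 apply to both arms (Follow-up). A control who misses an infusion or a sample leaves the set. This stands. A reader might infer that poor-prognosis patients are lost from the algorithm arm alone, but the text supports only preferential loss.
- **Some expected non-completers never enter.** The Exclusion criteria bar patients who refuse the algorithm's recommendation or are judged unable to receive the regimen. This narrows the problem but cannot remove it. The score uses day-15 albumin and creatinine, so a patient's final recommendation is not known at screening.
- **The primary conclusion is not shown to be at risk.** This stands. Imputation for the primary objective is tied to ITT, and patients who discontinue are to be kept under evaluation to allow ITT analyses. Nothing makes per-protocol primary or lets it override ITT. A reader might infer that a biased per-protocol result could rescue a failed trial, but that is speculation about reporting.
- **The size is assumed.** This also stands. The document gives no completion rate and no remission rate by risk class, and at modest non-completion the bias is under one point. Non-completers doing worse than their class is plausible rather than established.
- **Covariates for a supportive analysis belong in the SAP, which is not shown.** That is fair for the adjustment itself, whose absence is not the finding. The definition that creates the imbalance is fixed in this document.

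The treating nephrologist may also override the algorithm (Experimental strategy). The definition does not say whether an overridden patient has completed the schedule, so such a patient's per-protocol status is open. It cannot be assumed that they are excluded.

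**Conclusion.** The concern holds in a limited form. The completion condition is unequal between arms and linked to prognosis, so the per-protocol comparison is expected to favour the algorithm arm. The ITT analysis is untouched.

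Under the stated assumptions the spurious difference is about +0.4 to +3 points, and about +1 to +7.5 points if non-completers do markedly worse than their risk class. Against a planned 25 points this is small to moderate. The upper end needs both 30% non-completion and 20% remission among non-completers, and the document supports neither figure. It is worth correcting because the correction is cheap.

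**What to change.** State that the per-protocol analysis is supportive to ITT. Adjust it for the algorithm score, stratify it by risk class, or standardise it to the score distribution in the ITT population. Compute the score from day-0 and day-15 values in both arms. The day-15 visit covers all patients, and the secondary endpoints already evaluate the algorithm in controls. State also which schedule counts as completed when the nephrologist overrides the recommendation.

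The cost is some wording and one covariate or stratification factor. The score is then needed for every per-protocol patient, and the result is no longer a raw 2×2 comparison. The adjustment removes only the between-class part of the bias. The report should say that selection within a risk class may remain, and should give completion by arm and risk class so that readers can judge it.

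An alternative is to define completion in both arms by the two shared infusions and report the added ones separately. That makes the condition symmetrical, but it counts patients who missed planned infusions as per-protocol, so the set no longer estimates the effect of the completed strategy. This trade-off is debatable, and the score-based route is preferable.
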